#### Study procedure

Participants will accept anthropometric measuring by clinicians from the three collaborating hospitals, including Bo Ai Hospital of Zhongshan, People’s Hospital of Qu Fu, and Da Lian Children’s Hospital. The cohort study was scheduled to begin in October, 2019, and the first and secondary follow-up visits will be conducted one and two years later, respectively. A flowchart of the study design was shown in Fig. 1, and the investigation contents required at baseline, first visit, and second visit were shown in Table 1.

**Fig. 1 Fig1:**
[figure not shown]
Flow chart of the prospective cohort study

**Table 1 Tab1:** The investigation content required at baseline, follow-up of the prospective cohort study

Items	Baseline	First visit	Second visit
**Children’s health and family environment questionnaire (all participants)**			
Lifestyle	√	√	√
Family environment	√	√	√
Parental information	√	√	√
Early life information	√	√	√
**Physical examination (all participants)**			
Anthropometric measures	√	√	√
Sexual development	√	√	√
**Biological samples (participants selected for case-control study)**			
Blood	√		
Urine	√	√	√
Feces	√		
**Laboratory examination (participants selected for case-control study)**			
Endogenous hormones	√	√	√
Genes	√		
EEDs	√		
Gut microbiota	√		

*EEDs* Environment endocrine disruptors

### Data collection

#### Genotyping and SNP selection

Due to differences in gene polymorphism distribution in different ethnic groups, we screened ten candidate genes and selected one or two representative single-nucleotide polymorphisms (SNPs) each gene on the basis of the Hans according to GWAS database (www.genome.gov/gwastudies) and the related literatures, the candidate genes and SNPs were shown in Table 2.

**Table 2 Tab2:** The characteristics of candidate gene associated with obesity and precocious puberty

Gene	Chr	SNP1	SNP2
*ADCY3*	2p23.3	rs6752378	rs713586
*BDNF*	11p14.1	rs4923461	rs7481311
*FTO*	16q12.2	rs1121980	rs1558902
*KCTD15*	19q12.1	rs29941	rs287103
*LEP*	7q32.1	rs104894023	rs724159998
*NEGR1*	1p31.1	rs2568958	rs2815752
*SEC16B*	1q25.2	rs10913469	rs543874
*TMEM18*	2p25.3	rs4854344	rs2867125
*TNNI3K*	1p31.1	rs1040070	rs1514175
*MC4R*	18q22	rs663129	rs12970134

#### Physical examination

Anthropometric data, including weight (kg), height (cm), and waist circumference (cm), will be measured for each child standing without shoes and lightly clothed using standard techniques by one observer at baseline and the first and second visit. Waist circumference will be measured midway between the lower edge of the rib and the upper edge of the ilium. All of the measurement indexes will be measured twice and averaged. Overweight and obesity are the main predictors of interest and will be defined by BMI value, which is calculated as weight (kg) divided by height squared (m^2^). Participants will be defined as normal weight, overweight, or obese if their BMI index is between 18.5 and 25 kg/m^2^, greater than 25 kg/m^2^, or greater than 30 kg/m^2^, respectively, according to the age- and sex-specific cutoff standard for 2- to 18-year-old children proposed by the International Obesity Task Force (IOTF) [24, 25]. Children with overweight or obesity and some participants with normal weight (matched for sex and age with children with obesity and overweight) will be recruited to analyze their body composition, including height, weight, fat-free mass, body fat mass, body fat rate, body water, muscle mass, basal metabolic rate, total energy consumption, protein, inorganic salt, and impedance.

#### Sexual development assessment

The primary outcome is the difference in incidence of precocious puberty between normal-weight and obese children.

Secondary sexual characteristics assessment for boys and girls will be conducted by male and female professional pediatric endocrinologists or pediatric care physicians separately in different rooms to protect the children’s privacy. Breast development will be evaluated by visual inspection and palpation. Girls with overweight or obesity will be subjected to breast ultrasound to evaluate their nodules. In boys, testicular volume (TV) will be determined by palpation and an orchidometer. According to Marshall and Tanner [26, 27], breast and pubic hair development are divided into 5 stages (stages I to V). Precocious puberty will be diagnosed according to the Tanner stage: onset of breast development stage II (B_2_) or pubic hair development stage II (PH_2_) or above before 8 years or menarche before 10 years of age in girls, and PH_2_ or testicular enlargement (TV ≥ 4 ml) before 9 years of age in boys [28–30].

The presence of early puberty will be defined as children reaching a certain stage of puberty earlier than the median age of that stage [31]. According to previous studies, the median age of puberty onset (girls: breast or pubic hair development; boys: pubic hair or testicular volume development) of Chinese adolescents will be referenced [32, 33], and the onset of menarche before 12 years of age in girls and of voice breaking before 13 years of age in boys will also be defined as early puberty [34].

We separately evaluated the tanner stage for each breast among obese girls by using portable ultrasound (US), and chose the larger one as evaluation result. Tanner II by US is characterized as the presence of a hyperechoic retro-areolar nodule with a central star-shaped or linear hypoechoic area, this stage is assumed to mark the start of breast development [35].

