**Methods:**

We will conduct a multi-center prospective cohort study in three cities, which are selected in southern, central, and northern China, respectively. Primary schools in these cities will be selected by a stratified cluster random sampling method. Primary school students from grade 1 to grade 3 (6 to 10 years old) will be selected for the cohort with extensive baseline data collection, including assessment of pubertal development, family demographic information, early development, sleep pattern, dietary pattern, and physical activity. Participants will be followed up for at least three years, and long-term follow-up will depend on future funding.

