## Methods

### Study design, setting, and participants

#### Study design and sampling

This study is a prospective multi-center cohort study sponsored by the Shanghai Children’s Medical Center affiliated to the School of Medicine, Shanghai Jiao Tong University and performed in three cities in southern, central, and northern China, namely, Zhongshan, Guangdong Province, Qufu, Shandong Province, and Dalian, Liaoning Province. According to socioeconomic level and geographical distribution, the districts of Zhongshan, Qufu, and Dalian are stratified into urban districts in the central area and suburban districts in suburban areas. Using a stratified cluster random sampling method, districts and schools will be selected according to geographical location and school size by a random number generator. Grade 1, 2, and 3 children (6 to 10 years old) from primary schools will be included in this study. However, participants with overweight or obesity with a history of hormone treatment in the past 6 months as reported by parents in the questionnaire will be excluded.

We will carry out a nested case-control study, which will be nested in this cohort study. Participants in case-control study will be enrolled in four groups: children with normal weight and normal puberty, with normal weight and precocious puberty, with overweight/obesity and normal puberty, and with overweight/obesity and precocious puberty. And they will be measured body composition, collected venous blood, and stool at baseline, and collected urine samples at baseline and follow-up periods.

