### Data analysis

Categorical variables will be reported as the number and percentage and analyzed by a chi-square test to compare the distribution between groups. The *t*-test, analysis of variance, and Wilcoxon rank-sum test will be used to compare the differences in distribution of continuous variables, which will be described by mean ± standard deviation (*SD*) for normal data or median with interquartile range for non-normal data.

Based on the discovered pleiotropic genes and obesity-related risk loci (SNPS), we will examine the distribution of gene polymorphisms (SNPS). For obesity-related SNPs of these genes, Effect size Weighting was carried out according to the method reported by Speliotes EK et al. [40], and then genetic risk scores (GRS) will been calculated using the method established in our previous study [41].That is, the number of effective Allele genes (Allele) was calculated, then the weighted value was multiplied, and finally the combined GRS of SNPs of all candidate genes in this study was accumulated.

The effects of exposure factors on outcomes will be evaluated after adjusting confounding factors using logistic regression or multiple linear regression. To analyze whether there is a linear trend of GRS among four groups: children with normal weight and normal puberty, with normal weight and precocious puberty, with overweight/obesity and normal puberty, and with overweight/obesity and precocious puberty, the Cochran–Mantel–Haenszel Trend Test will be used. After 3 years’ follow-up, a causal relationship model between exposure factors and outcomes will be established by using Mendelian randomization (MR) and Egger’s regression models and assessed by sensitivity analysis. Statistical analyses will be performed by using IBM SPSS, STATA and R statistical packages. and the level of significance will be set at *p* < 0.05.

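### The primary outcome is incidence of an age-limited condition, but the risk set is not defined and yearly exams leave onset around the age limits unresolved

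*Protocol article*

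**What the plan says.** The section Sexual development assessment sets the endpoint: "The primary outcome is the difference in incidence of precocious puberty between normal-weight and obese children". It then defines precocious puberty by age at onset. For girls the signs are breast or pubic hair stage II "or above before 8 years or menarche before 10 years of age in girls". For boys they are PH2 or "testicular enlargement (TV ≥ 4 ml) before 9 years of age in boys".

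Study design and sampling fixes the population: "Grade 1, 2, and 3 children (6 to 10 years old) from primary schools will be included in this study". The one exclusion given there is for overweight or obese children whose parents report recent hormone treatment. Nothing is said about children who already show pubertal signs at the first exam.

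Study procedure states that "the first and secondary follow-up visits will be conducted one and two years later, respectively", and Table 1 lists baseline and two visits. The abstract, however, says "Participants will be followed up for at least three years", and Data analysis places the causal modelling after three years of follow-up.

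For the analysis the article says: "The effects of exposure factors on outcomes will be evaluated after adjusting confounding factors using logistic regression or multiple linear regression". The planning rates under Sample size (4.85% and 8.43%) are described there as prevalences in children aged 7 to 10 years.

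**The concern.** Incidence needs a set of children who are free of the condition and still able to develop it. Here the age limits in the case definition fall inside the entry age range, so many enrolled children do not meet that requirement:

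- A girl aged 8 or more can be a new case only by menarche before 10. A boy aged 9 or more cannot be a new case.
- A child below the limit who shows the sign at baseline is a prevalent case. A child past the limit who shows it at baseline has an unknown onset age.
- A girl negative at 7.6 and positive at 8.6 had onset on one side of 8 or the other, and age at exam does not say which. A plain yes/no outcome in a binary regression has no place for her.

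If all these children enter one comparison, the reported incidence depends on the age mix at entry and on how many were already pubertal. Prevalent cases also weaken the causal reading, because weight measured at baseline may then follow puberty rather than precede it. The planning rates are prevalences too, so the sample size does not describe the quantity named as primary.

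**Working it through.** **1. The plan's own figure.** Inputs (Sample size): p1 = 0.0843, p2 = 0.0485, difference d = 0.0358, α = 0.05, power 90%, loss 15%.
- One-sided two-proportion formula: n = 827 per group. With continuity correction, (n/4)·[1 + √(1 + 4/(n·d))]² = 882.
- 882/0.85 = 1038 per group, and 4 × 1038 = 4152, the stated number per centre. The factor 4 (two weight groups, doubled again, presumably by sex) and the continuity correction are inferred from the match and are not stated.
- The printed formula with u = 1.96 gives 1013 per group, 1193 after loss and about 2385 for two groups, so it does not give 4152 directly.

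**2. Who is past the limit at entry (Table 3, Qufu and Zhongshan only).**
- Girls 8 to under 11: 1628/3993 = 40.77%. Girls 6 to under 8: 2365/3993 = 59.23%.
- Boys 8 to under 11: 1809/4630 = 39.07%. The table has no cut at 9, so the share of boys past their limit cannot be computed.

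**3. What the visits can show (exams at exactly 0, 1 and 2 years).**

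| Entry age | Age at visit 1 | Age at visit 2 | Girls: follow-up exam under 8? | Boys: follow-up exam under 9? |
|---|---|---|---|---|
| 6 to <7 | 7 to <8 | 8 to <9 | visit 1 only | both visits, never seen at 9 |
| 7 to <8 | 8 to <9 | 9 to <10 | none | visit 1 only |
| 8 to <9 | 9 to <10 | 10 to <11 | past 8 at entry | none |

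No girl is under 8 at visit 2. Table 3 does not split the 6-to-8 band. If 30% to 60% of it is under 7 (assumption), then 0.30 × 2365 = 710 to 0.60 × 2365 = 1419 girls, or 18% to 36% of all 3993, can be seen newly positive for B2/PH2 while under 8. For girls aged 7 to under 8 at entry, a first positive exam always comes after the limit.

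**4. Power on an age-eligible set (illustration).** Take completers 4152 × 0.85 = 3529 per centre, with Table 3 shares of 21.79% overweight or obese and 62.57% normal weight (obesity alone is not tabulated). Use power = Φ[(d − 1.96·se0)/se1], with se0 the pooled and se1 the unpooled standard error.
- All ages: 769 v 2208, power 93.5%.
- Girls under 8 plus boys under 9, assuming 30% to 90% of the 1809 older boys are under 9: (2365 + 2821 + 0.30 × 1809)/8623 = 66.4%, up to (2365 + 2821 + 0.90 × 1809)/8623 = 79.0%.
- Groups of 511 v 1467 give 81.9%; 608 v 1745 give 87.5%. At one-sided 0.05 the range is 88.3% to 92.4%.
- Three centres pooled, two-sided: 99.8% to 99.9%.

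These figures treat the planning prevalences as incidences and do not subtract children already pubertal, whose number is not given.

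**The case against.** The strongest reply is that a journal article condenses a protocol, and that at-risk sets and censoring rules usually sit in the full protocol or analysis plan. Part of this stands. The absence of an exclusion does not prove that prevalent cases will be kept. Two of the nested groups have precocious puberty and give blood and stool at baseline, which suggests that such children are in the cohort. But the biospecimen section selects children by weight status, so the four groups could be formed later. What the reply does not remove is the mismatch within the text between an incidence endpoint with age limits of 8 and 9, entry at 6 to 10, and planning rates that are prevalences.

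Several stronger readings are tempting and are not supported:

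- **That the 3.58-point difference shrinks by 40%.** Multiplying by the under-8 share (0.0358 × 0.6014 = 0.0215) treats the planning figure as coming from under-8s. It comes from ages 7 to 10, a band that already includes children past the limits, so the scaling dilutes it twice.
- **That per-centre power is 78%, or 51%.** The first applies the under-8 share to both sexes although the boys' limit is 9. The second also halves the rates without any basis in the document.
- **That children aged 8 or more contribute no cases.** Girls of 8 to under 10 can qualify by menarche, and boys of 8 to under 9 are still at risk.
- **That logistic regression is the fault.** It is named for exposure effects in general, not for the primary outcome, and would be acceptable for cumulative incidence in a defined risk set. Nor does the article say that onset will be scored by age at exam.

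**Conclusion.** The point holds and concerns the primary outcome. Followed as written, the plan does not yield an interpretable incidence: the risk set is undefined, 40.77% of girls in two of the three cities are past the B2/PH2 limit at entry, and onset near the limits is interval-censored with nothing stated to handle it. The conflict between visits at one and two years and a follow-up of at least three years is separate and plain on the page.

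The harm is mainly to validity rather than to power. The direction and size of the bias cannot be computed, because the article gives neither the number pubertal at baseline nor the age distribution within bands. The visit-timing result assumes exams exactly one and two years after baseline. The 18% to 36% and 82% to 88% ranges rest on the assumed age splits and are illustrations.

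**What to change.** Using the document's own age limits:

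1. **Risk set.** For the primary incidence analysis, define it by sex and criterion, free of the sign at baseline: B2/PH2 in girls under 8, PH2 or testicular volume in boys under 9. Treat menarche before 10 as a separate component, in girls under 10 and premenarcheal at entry, so that this criterion is not lost for girls aged 8 or more. Take weight group at baseline as the exposure.
2. **Everyone else.** Report children already pubertal at baseline, or past the limit, separately as baseline prevalence or as unknown onset age.
3. **Analysis.** Analyse age at onset as interval-censored between the last negative and the first positive exam, and report cumulative incidence by the age limits. Enter children pubertal at baseline as left-censored only in a sensitivity analysis, because their baseline weight may follow puberty.
4. **Follow-up.** Reconcile Study procedure and Table 1 with the abstract and Data analysis. Censor boys not yet 9 at the last exam.
5. **Sample size.** State that the planning rates are prevalences in ages 7 to 10, and restate power on the actual risk set.

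The cost is mostly wording, since pubertal staging is already scheduled at every visit. The analysed set becomes smaller and the stated per-centre power falls, while pooled power stays high at the planning rates. If the reconciliation settles on three years, an additional visit would need to be scheduled.

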## Discussion

In this protocol, we described the study design, data collection methods, and analysis of a prospective cohort study in a population-based primary school children. According to the geographical distribution, we chose three cities in northern, central, and southern China and did our best to carry out this study to ensure the representativeness of the population. Students in grades 1 to 3 in randomly selected primary schools are expected to represent local school-age children.

By collecting information on factors such as children’s family environment, lifestyle, and genes, this study will analyze the effect of these factors on children’s physical development from the perspectives of heredity and environment. As a longitudinal study, this study will start earlier in development than previous studies to capture the impact of early childhood experiences on puberty development. Puberty is defined through visual and palpation inspection by a clinical doctor combined with ultrasonic diagnostics; previous studies have depended on self-reports or clinical palpation by non-professional volunteers, which are less sensitive and precise measurements, especially for breast development assessment among obese girls, which may lead to overestimating the precocious puberty detection rate among obese girls, since it is difficult to distinguish adipose tissue and breast tissue, so we will use ultrasonic examination in this study. Although the relationship between obesity and the sexual development of children has been confirmed in both genders by many earlier studies, due to the racial differences in the influence of obesity on sexual precocity, the relationship between obesity and early development is controversial among boys. Through this prospective cohort study, we will further investigate the relationship between obesity and development among Chinese mainland children.

To expand the previous research on puberty development, this study starts from the gene pleiotropy of obesity and takes the lead in studying the influence of the genetic polymorphism of obesity on precocious puberty. Although studies on genetic polymorphism of obesity or precocious puberty in girls have been performed previously, there has been no report on the combination of the two phenotypes, which is expected to reveal the genetic mechanism of the association between childhood obesity and precocious puberty.

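### The breast criterion is staged with ultrasound only in heavier girls, so misclassification of the primary outcome in girls can differ by exposure

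*Protocol article*

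**What the plan says.** All statements on method are in the Protocol article, section Sexual development assessment.

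- Primary outcome: "The primary outcome is the difference in incidence of precocious puberty between normal-weight and obese children".
- General method for breast stage: "Breast development will be evaluated by visual inspection and palpation".
- Additional method, first sentence: "Girls with overweight or obesity will be subjected to breast ultrasound to evaluate their nodules".
- Additional method, second sentence: "We separately evaluated the tanner stage for each breast among obese girls by using portable ultrasound (US), and chose the larger one as evaluation result". Ultrasound stage II has its own criterion, a retro-areolar nodule, and "this stage is assumed to mark the start of breast development".
- In girls, breast stage II or above before 8 years is one of three alternative criteria for precocious puberty. The others are pubic hair stage II or above before 8 years and menarche before 10 years.

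The Discussion gives the reason for ultrasound. Without it, fat tissue can be mistaken for breast tissue, "which may lead to overestimating the precocious puberty detection rate among obese girls". No ultrasound is described for normal-weight girls.

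**The concern.** The method that settles one criterion of the primary outcome depends on the exposure being studied. If ultrasound finds breast tissue that the hand misses, only the heavier girls gain cases. If ultrasound rejects breast tissue that the hand wrongly reports, only the heavier girls lose cases. Either way the error rates of the outcome can differ between the compared groups, and a larger sample does not remove that kind of bias.

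Two details add to it. One sentence scans girls with overweight or obesity, the other only obese girls, so the exposed group may itself mix methods. The rule of taking the larger breast is stated only for ultrasound.

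The effect can travel further. The four nested case-control groups are defined by weight status and precocious puberty (Study design and sampling), and the trend in genetic risk score is tested across them (Data analysis).

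**Working it through.** The plan gives no figure for this point, so there is none to reproduce. The question is how large the bias could be in the contrast the plan actually defines, which is among all children.

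**Inputs from the document**

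- Sample size section: 4.85% in normal-weight and 8.43% in overweight children, a difference of 3.58 points.
- Table 3 (Zhongshan and Qufu, baseline): 2594 of 5395 normal-weight children are girls, 2594/5395 = 0.481.
- Table 3: 679 of 1879 children with overweight or obesity are girls, 679/1879 = 0.361.
- Table 3: 2365 of 3993 girls are under 8, 2365/3993 = 0.592.

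**Assumptions, not in the document**

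- Ultrasound makes no errors, and true incidence is 4.85% in both groups.
- Every case in girls arises through breast stage. This is an upper bound, because cases by pubic hair or menarche are measured alike.
- The age mix of all girls holds within each weight group.

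With error-free ultrasound, all the error lies in the palpated normal-weight girls. The girls-only bias therefore carries into the all-children contrast with weight 0.481.

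**Missed cases.** False excess in girls = 0.0485 × (1 − sensitivity). In all children, multiply by 0.481.

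| Palpation sensitivity | Girls, points | All children, points | Share of 3.58 |
|---|---|---|---|
| 90% | 0.49 | 0.23 | 7% |
| 80% | 0.97 | 0.47 | 13% |
| 70% | 1.46 | 0.70 | 20% |

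**False positives.** Breast stage II counts only before 8 years. False deficit in all children at baseline = 0.9515 × false-positive rate × 0.592 × 0.481.

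| Palpation false-positive rate | Girls under 8, points | All children, points |
|---|---|---|
| 1% | 0.95 | 0.27 |
| 2% | 1.90 | 0.54 |
| 3% | 2.85 | 0.81 |

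The two errors work in opposite directions. At 80% sensitivity and 2% false positives they nearly cancel: 0.47 − 0.54 = about −0.1 points. If both methods had the same sensitivity and specificity, the false difference under equal incidence would be zero.

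**The case against.** The strongest defence is that the asymmetry is deliberate and explained. The Discussion says palpation misleads in obese girls, so palpation error already depends on exposure and ultrasound is there to reduce it. Unequal procedures need not mean unequal accuracy. This stands as a reason to scan obese girls. It does not show that ultrasound in one group and palpation in the other are equally accurate.

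The same argument tells against making palpation the primary method for everyone. Suppose palpation gives 5% false positives in obese girls and 1% in normal-weight girls. The false excess among girls is 0.9515 × 0.04 = 3.8 points, before any restriction to those under 8. In the all-children contrast at baseline it is 0.9515 × 0.592 × (0.05 × 0.361 − 0.01 × 0.481) = about 0.7 points, similar to the largest values in the working. So a palpation-only result belongs beside the ultrasound-informed one, not in its place.

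It can also be said that the text does not discard palpation in scanned girls; the Discussion speaks of clinical examination combined with ultrasound. That is fair, although "chose the larger one as evaluation result" points to ultrasound as deciding. A rule for discordant readings and a sensitivity analysis may sit in a fuller protocol or analysis plan, so their absence from a condensed article is not held against it. The measurement rule itself is printed here, and it is unequal.

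**Conclusion.** The point holds as a limitation of the primary comparison in girls. One criterion of the outcome is measured by a method that depends on exposure, and the bias can go either way. Under the stated assumptions it amounts to a false excess of about 0.2 to 0.7 points or a false deficit of about 0.3 to 0.8 points in the all-children contrast, against a planned difference of 3.58. The size rests wholly on assumed accuracies. Errors in ultrasound itself would add to or offset these figures.

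Three stronger readings are tempting and are not supported.

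- A reader might infer that breast stage is the main route to a case in girls. The document gives no breakdown by criterion.
- A reader might set the girls-only bias of 0.5/1.0/1.5 points against 3.58 and report 14/27/41%. The 3.58 points refer to all children, of whom girls are about half in the normal-weight group, and false positives count only under 8.
- A reader might infer that the obesity difference could be reversed. The largest shift in the working is about 0.8 points, which does not reverse a true difference of 3.58.

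The disagreement between the two sentences on which girls are scanned is a plain inconsistency, whatever the size of the bias.

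**What to change.** Keep the ultrasound-informed stage, and make these changes.

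1. Record the inspection-plus-palpation stage as a separate field for every girl. This can be done prospectively in Dalian, whose baseline was scheduled for December 2022 (Study status), and at remaining visits elsewhere. For completed visits in Zhongshan and Qufu, use it where it was kept.
2. Apply the larger-breast rule under both methods.
3. Prespecify that the contrast is reported (a) with ultrasound-informed stage, (b) with palpation stage in all girls, and (c) on criteria assessed alike in both weight groups: pubic hair stage or menarche in girls, and boys separately.
4. If (a) and (b) differ materially, state that the result in girls depends on the measurement method.
5. Reconcile the two sentences on which girls are staged by ultrasound.

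The cost is one recorded field and two further analyses; no new examination is needed, because palpation is already described for breast assessment generally. The drawbacks are that (b) carries the fat-tissue error the Discussion describes, (c) has fewer events, and completed visits can enter (b) only if the palpation stage was retained.

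### For the additional outcome of early puberty, the age limits for menarche (12) and voice breaking (13) lie beyond the observation window for most children, so a yes/no outcome cannot separate 'not early' from 'not yet old enough'

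*Protocol article*

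**What the plan says.** All references are to the protocol article.

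- **Definition.** Sexual development assessment gives a general rule for early puberty, "children reaching a certain stage of puberty earlier than the median age of that stage", and adds two fixed limits: "the onset of menarche before 12 years of age in girls and of voice breaking before 13 years of age in boys will also be" classed as early puberty. For pubertal onset it points to published Chinese medians but does not state them.
- **Entry age.** Study design and sampling: "Grade 1, 2, and 3 children (6 to 10 years old) from primary schools will be included in this study". In Table 3 the oldest age band ends below 11.
- **Follow-up.** Study procedure: "the first and secondary follow-up visits will be conducted one and two years later, respectively". Table 1 has the same three time points. The abstract differs: "Participants will be followed up for at least three years, and long-term follow-up will depend on future funding". Data analysis also speaks of three years of follow-up before the causal modelling.
- **Analysis.** Exposure effects on outcomes are to be estimated, after adjustment for confounders, "using logistic regression or multiple linear regression". No time-to-event method is named.
- **Place of this outcome.** The primary outcome, the four case-control groups and the cohort sample size all rest on precocious puberty, which has its own, lower age limits.

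**The concern.** A rule of the form 'event before age A' gives a definite yes as soon as the event is seen. It gives a definite no only once the child has been observed to age A without the event. If follow-up stops earlier, the answer is unknown: a girl last seen at 9 without menarche may still have it at 11.

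The model type named in the article needs a yes or a no for every child analysed, and the article has no rule for a child who is event-free and still below the limit. If such children were entered as 'no', older entrants would have more chance to become a 'yes' than younger ones. The outcome would then partly measure age at last visit, and hence grade at entry. Some future early maturers would sit in the comparison group.

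**Working it through.** The plan states no figure on this point, so there is none to reproduce beyond the Table 3 percentages.

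**Inputs**
- Age limits: 12 (menarche) and 13 (voice breaking), from Sexual development assessment.
- Follow-up F: 2 years (Study procedure, Table 1) or 3 years (abstract, Data analysis).
- Ages at entry, Table 3 (Zhongshan and Qufu). Girls: 2365 of 3993 under 8 (59.23%) and 1628 aged 8 to under 11 (40.77%). Boys: 2821 of 4630 (60.93%) and 1809 (39.07%). The percentages recompute correctly.

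**Step 1: entry age needed to be observed to the limit** = limit − F
- Menarche: 12 − 2 = 10, or 12 − 3 = 9.
- Voice breaking: 13 − 2 = 11, or 13 − 3 = 10.

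**Step 2: bounds that need no assumption about ages within a band**
- Boys, 2 years: entry at 11 or older is needed and every boy is under 11, so 0 of 4630 reach 13.
- Boys, 3 years: nobody entering under 8 qualifies, so at least 60.93% fall short.
- Girls, 2 or 3 years: nobody entering under 8 qualifies, so at least 59.23% fall short.

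**Step 3: point estimates, assuming uniform ages from 8 to under 11**

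| Marker | F | Share of older band old enough | Number reaching the limit | Share of that sex | Not reaching |
|---|---|---|---|---|---|
| Menarche, 12 | 2 | 1/3 | 1628/3 ≈ 543 | 13.6% | 86.4% |
| Menarche, 12 | 3 | 2/3 | 1628 × 2/3 ≈ 1085 | 27.2% | 72.8% |
| Voice, 13 | 2 | 0 | 0 | 0% | 100% |
| Voice, 13 | 3 | 1/3 | 1809/3 = 603 | 13.0% | 87.0% |

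These counts are before any loss to follow-up.

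**Step 4: what this means for the definition.** On the two-year schedule every boy is below 13 throughout. The voice-breaking limit therefore does no work: each observed voice break counts as early, and no boy can be shown to be 'not early' on this sign. For menarche, a firm 'no' is available only for the minority in the table. A third year raises these shares but still leaves most children of each sex undetermined unless the event has been seen.

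**The case against.** Several points on the other side stand.

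- **The coding is not in the text.** The article never says that event-free children below the limit count as 'not early', and a separate analysis plan could hold a rule. This stands. What remains is that the stated definition, with the stated schedule, leaves most non-events undetermined whatever coding is chosen.
- **Bias toward zero.** A reader might infer that mixing future early maturers into the comparison group must dilute effects. The documents do not support this. Take menarche as normally distributed with means 12.5 and 12.0 years and SD 1.2 (assumed values, not from the documents). The odds ratio is 1.95 with everyone observed to 12, 2.15 to 11 and 2.65 to 10, so truncation can enlarge an odds ratio.
- **Adjustment for age.** The planned confounder adjustment could include age. That would reduce confounding by age at entry, but it cannot supply the missing status.
- **The median rule.** A reader might also object that a median cut-off makes about half of a reference population 'early'. That is true by definition, but it is an explicit, cited choice, and abnormal timing is covered separately by precocious puberty. Renaming the category would be a matter of preference. Because the onset medians are not stated, the argument about the observation window cannot be extended to breast, pubic hair or testicular onset.
- **Limited reach.** Early puberty is an additional classification, and the article specifies no analysis for it by name. This keeps the point below the level of a threat to the main result.

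**Conclusion.** The point holds for the two fixed age limits. With visits to year 2, no boy is observed to 13 and at least 59% of girls are not observed to 12. With three years, at least 61% of boys and 59% of girls still fall short. A yes/no outcome on these signs would depend on age at last visit; the direction of the effect on exposure estimates is open.

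The bounds rest on the Table 3 ages for two of the three cities, and on visits at their nominal intervals; a late visit could carry a few of the oldest boys past 13. The figures of 86% and 73% (girls, two and three years) and 87% (boys, three years) also assume uniform ages within the older band.

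It would be wrong to conclude that the primary outcome is compromised: precocious puberty does not use these limits. The plan should be corrected on this point before early puberty is analysed.

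**What to change.** 1. Analyse age at reaching each marker (B2, PH2, testicular volume of 4 ml or more, and menarche and voice breaking where recorded) as interval-censored time-to-event data with age as the time scale. Children already at the stage at baseline are left-censored; those not there at the last visit are right-censored; the others lie between two visits.
2. If a yes/no version is kept, include only children whose last visit is at or after the age limit. Apply that restriction to events and non-events alike, so that selection does not depend on the outcome. Do not use the voice-breaking criterion under two-year follow-up.
3. Reconcile the two-year schedule (Study procedure, Table 1) with the three-year follow-up (abstract, Data analysis), because the number of children reaching each limit depends on it.
4. Confirm that menarche status or age is recorded at each visit. It is not among the four items listed for girls in the adapted Pubertal Development Scale; voice breaking is listed for boys as a parent rating.

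**Cost.** Table 1 already has sexual development examined at all three visits, so the examined stages need no new visits, only somewhat more analysis work. Menarche may need an added question. Results would be expressed as differences in timing rather than percentages, and any yes/no version would keep few children: on the uniform-age assumption, about 543 girls and no boys at two years.
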